### Trial design

This study is a two-arm single-blinded randomized controlled trial of an individually tailored multicomponent intervention (see Table 1) for older men and women living in nursing homes. The study will be aptly named PROCARE – Prevention and occupational health in long-term care, as part of the PROCARE project. A stratified randomization is performed after the baseline assessment. The assessment of primary and secondary outcomes takes place in all subjects upon entry to the study (T1) by a blinded assessor and is repeated at 16 weeks (T2), and at 32 weeks (T3, retention test, intervention group only) after randomization (see Table 2). *The trial is registered at DRKS.de with registration number* DRKS00014957.

**Table 1 Tab1:** Description of the intervention

Program	Week 1–4	Week 5–8	Week 9–12	Week 13–16
Mobilisation and warm-up	e.g., range of motion exercises for the wrists, hip, shoulders, knees, and ankles	Cf. week 1–4	Cf. week 1–4	Cf. week 1–4
Coordination, balance, and cognitive exercises	e.g., standing balance, bodyweight shifting, motivational cognitive-motor games with group interaction including balls and scarfs	e.g., standing balance, bodyweight shifting, motivational cognitive-motor games with group interaction including balls and scarfs	e.g., standing balance with feet together, side-by-side, bodyweight shifting, motivational cognitive-motor games with group interaction including balls and scarfs	e.g., standing balance with feet together, side-by-side, semi-tandem, tandem, standing on one leg, bodyweight shifting, motivational cognitive-motor games with group interaction including balls and scarfs
Dual-task walking exercises (endurance)	150-180 m e.g., brisk walking, starting, stopping, avoiding obstacles, turns	180-240 m e.g., brisk walking, starting, stopping, avoiding obstacles, turns	240-300 m e.g., brisk walking, starting, stopping, avoiding obstacles, turns, dual-task conditions e.g., carrying a cup, repeating rows of numbers, paying attention to signs	300-330 m e.g., brisk walking, starting, stopping, avoiding obstacles, turns, dual-task conditions e.g., carrying a cup, repeating rows of numbers, paying attention to signs
Calm down	e.g., stretching and relaxing exercises	Cf. week 1–4	Cf. week 1–4	Cf. week 1–4

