#### Assignment of interventions

Assessment and data collection will be done by blinded assessors in a strictly pseudonymized form to guarantee a blinded data analysis.

To avoid performance bias, the measurements and the intervention follow a standardized protocol. All participant information and data will be stored securely and identified by a coded ID number only to maintain the participants’ confidentiality.

To avoid selection bias, a stratified randomization will be conducted to divide the participants into either an intervention group or a waiting time control group. The random allocation will be stratified and executed by lot by the director of the study who will receive the pseudonymized codes of the participants and their baseline characteristics and will not be involved in neither the assessment nor the intervention procedures. Stratification will be based on comparable sex, age, and cognitive performance (according to the Montreal Cognitive Assessment MoCA-Score [44]) to avoid differences in the baseline characteristics of the groups. After assigning the participants to either the intervention or waiting time control group, the pseudonymized participant codes will be sent to the study investigators who are responsible for the data management. The exercise scientist or physiotherapist, who will conduct the intervention, will receive only names of the participants in the intervention group and after 16 weeks names of the waiting time control group without being aware of the control group design.

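### The study director draws the allocation by lot with baseline characteristics in hand; this is a vulnerability in the draw, not shown bias, and cheap to close

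*Protocol article*

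**What the plan says.** Under Trial design the article fixes the timing: "A stratified randomization is performed after the baseline assessment". Under Assignment of interventions, in a paragraph that presents the procedure as the protection against selection bias, it fixes the method, the person and what that person holds:

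- Method, person and information held: the stratified allocation is "executed by lot by the director of the study who will receive the pseudonymized codes of the participants and their baseline characteristics".
- Separation of roles: the same sentence adds that the director "will not be involved in neither the assessment nor the intervention procedures".
- Strata: "Stratification will be based on comparable sex, age, and cognitive performance", the last measured by the MoCA, with the purpose "to avoid differences in the baseline characteristics of the groups". No categories or cut-points are given for age or MoCA.
- After the draw: "the pseudonymized participant codes will be sent to the study investigators who are responsible for the data management".

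The Monitoring section sets up no data monitoring committee. It gives an advisory board responsibility for data audits every 5 months and does not say whether these cover the draw.

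**The concern.** Randomisation protects the comparison only if the person who generates the allocation cannot influence, knowingly or not, which arm a participant with a given prognosis enters. Here the leader of the trial makes a manual draw on participants who have already been assessed, with their characteristics to hand. The codes hide who a resident is. They do not hide that resident's sex, age or cognitive score, which are needed for the stratification.

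The strata are also loosely fixed. Age and MoCA are numerical, and without stated categories it is open, on this text, who decides which residents count as comparable, and when. As far as the article goes, only the result of the draw is passed on, so a later reader could not tell one draw from several, or a random list from an arranged one. At stake is whether the trial could show afterwards that its arms were formed by chance.

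**Working it through.** No stated figure is in question, so the check sets the text against what each step would have to protect.

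**1. What each described safeguard covers.**

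- *Allocation after consent and baseline* (Trial design; Recruitment of participants). It protects enrolment and the baseline measurements from foreknowledge of the arm. It does not protect the draw, because the characteristics are known by then.
- *Director outside assessment and intervention* (Assignment of interventions). It protects measurement and delivery, and weakens any motive. It does not make the draw verifiable.
- *Pseudonymised codes* (same section). They conceal identity, but not the characteristics sent with the codes.
- *Data audits every 5 months* (Monitoring). They are not said to include the draw. Lots leave no sequence that can be regenerated, so an auditor would need a record made at the time, and none is described.
- *Covariate adjustment* (Statistical analysis). Baseline value, age, sex and education enter the model, which removes part of any measured imbalance. MoCA, a stratification factor, is not listed except as its own baseline when it is the outcome.

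**2. Two kinds of repeated draw.** Let D be the difference between arms in the mean of a baseline variable. Under one honest draw, D is symmetric about 0.

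- *Redraw until |D| is small.* The rule treats the arms alike, so the expected value of D stays 0 and the effect estimate stays unbiased. The spread of D shrinks, so conventional standard errors tend to be too large rather than too small.
- *Redraw, or arrange, until D favours one arm.* The expected value of D is no longer 0, and the comparison is biased to the extent that the variable is prognostic and not removed by adjustment.

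Only the second kind harms the result.

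**3. Illustration of the second kind.** Assumptions, none taken from the document: a simple 1:1 draw without strata, one baseline variable, the most favourable of k draws always kept, and no adjustment. In standard deviation units:

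SD(D) = √(4/n), and the expected D is the mean of the largest of k standard normal values × √(4/n).

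For one centre n = 140 (70 per arm, Sample size section), so √(4/140) = 0.169. For one draw over the whole trial n = 1120, so √(4/1120) = 0.060. By simulation:

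| k | n = 140 | n = 1120 |
|---|---|---|
| 1 | 0 | 0 |
| 2 | 0.10 | 0.03 |
| 5 | 0.20 | 0.07 |
| 10 | 0.26 | 0.09 |

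This is what deliberate steering could do on those assumptions. It does not estimate what will happen. Stratification and adjustment would reduce it for the factors they cover.

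**4. How fine the strata can be.** There are 1120/48 ≈ 23 residents per home. Two categories each of sex, age and MoCA make 2 × 2 × 2 = 8 cells, so about 23.3/8 ≈ 3 residents per cell within a home. Within a centre it is 140/8 = 17.5 per cell. Blocks by centre are workable. Blocks by home within all three factors would mostly be left incomplete.

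**The case against.** The case on the other side is substantial, and most of it limits the point rather than removing it.

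- *Drawing lots within strata is a legitimate random method.* This stands. Done once, it gives a valid allocation.
- *Whoever stratifies must know something.* This stands in part. Sex, age and MoCA are needed to form strata, but stratum labels would be enough for the draw. The article sends baseline characteristics without saying which. The Outcome measures section distinguishes demographic and baseline characteristics from outcomes, so the director may not see SPPB or gait values.
- *An article condenses a fuller protocol, which may hold a log, a witness rule and cut-points.* This stands for those details, and their absence alone would be no finding. But the article does state the method, the person and the information held, and that combination is what is questioned.

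A reader might infer three stronger things, and the text supports none of them. First, that the draw is unrecorded and cannot be audited: the article is silent on this, and a witnessed, logged draw could be checked. Second, that the director is instructed to arrange comparable groups: the sentence names the stratification factors and their purpose, and does not call for rearranging or redrawing. Third, that the standard errors would be invalid: for balance-seeking redraws the opposite tendency holds, as shown in the working, and nothing suggests redrawing to favour an arm.

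**Conclusion.** The point holds as a weakness in a stated procedure. Recruitment, assessment and delivery are reasonably shielded from the allocator. The draw is not, because it is manual, made by the trial's leader with prognostic characteristics visible and strata left open, and nothing described would allow it to be reproduced or checked.

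No bias is shown, and its size cannot be derived from the document. The illustrative shifts depend wholly on assumed misconduct and should not be read as an expected error. The conclusion assumes that no fuller document already provides a witnessed, logged draw with defined strata. If one does, a sentence saying so would settle most of the point. The change should be made because the whole comparison rests on this step, it cannot be repaired after allocation, and the remedy costs very little.

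**What to change.** Replace the lots with a computer-generated allocation, and say so in the protocol:

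- Define a few categories of sex, age and MoCA in advance, and use permuted blocks within those categories by centre. If balance by home is wanted, use minimisation with a random element instead of adding home as a further blocking layer.
- Lodge the seed and script before any baseline data are sent.
- Give the person who runs it participant codes and stratum labels only, not the other baseline characteristics.
- Run it once, treat the output as final, and keep a time-stamped log of the input, the output and any correction.

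Release by someone independent of the study lead would be preferable, but is not essential once the run is reproducible and logged. The cost is a short script and a protocol sentence. Sample size and staffing are unchanged.

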#### Recruitment of nursing homes

Eight cities and their surroundings throughout various regions in Germany (Bremen, Chemnitz, Frankfurt, Hamburg, Karlsruhe, Nuremberg, Paderborn and Stuttgart) will recruit 48 nursing homes in total (six per site). The institutions involved are deliberately selected based on their basic structural figures (number of nursing places, number of employees, urban or rural district, social-economic status), in order to analyze the applicability of the program under a wide range of conditions. Therefore, a list of all nursing homes will be created. It will then be stratified by their structural characteristics and afterwards the nursing homes will be randomly selected. Participation is voluntary and will not be remunerated. In case a requested nursing home declines to participate, another facility with similar characteristics will be requested instead.

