##### Physical functioning

The *Short Physical Performance Battery* (SPPB) [45] is a standardized instrument to test the lower extremity functionality (balance, gait speed, leg strength). Participants are required to show a stable stand in an upright position under three conditions (legs closed/feet together, semi-tandem stand, tandem stand). After that, comfortable gait speed will be assessed by measuring the time to walk a 4-m track, starting from a standing position and stopping when the first foot is past the 4-m line. Finally, a five times sit-to-stand transfer will be completed as fast as possible. Each domain is scored between 0 and 4 and SPPB overall scores range from 0 (low mobility/functionality) to 12 (full mobility/functionality). Clinically relevant improvements have been demonstrated to range between 0.99 and 1.34 points for the SPPB [45].

*Gait analysis* (GAITRite: CIR Systems Inc., Clifton, NJ, USA, Optogait: Microgate, Bolzano, Italy, MobilityLab: APDM Inc., Portland, USA, GaitUp: SA, Lausanne, Switzerland or Zebris PDM, Isny, Germany). Gait performance will be assessed by measuring step length, step width, gait speed, and double support phase on a 10-m track, using of one of the mentioned gait analysis systems. Each participant completes three trials: a test trial, one trial at preferred walking speed, and one trial at maximum walking speed. Measured data will be recorded and saved for later analysis by the gait systems software. An accompanying validation study will secure the comparability of the different gait measurement systems.

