### Intervention

The exercise program consists of 32 sessions for a period of 16 weeks. One training session has a duration of 45–60 min and takes place twice a week. Exercise sessions will be administered by at least one certified exercise scientist or physiotherapist with group sizes ranging from four to 15 participants. The program follows IAGG guidelines and combines previously published exercises that have proven to be beneficial for cognitive-motor performance in older people in the community and in need of care [7, 8, 12, 20, 35, 56–59]. Training focusses on daily situations which are commonly associated with an increased fall risk and it mostly includes challenging walking exercises (e.g., brisk walking, starting, stopping, avoiding obstacles, turns). During these exercises, participants are also exposed to a variety of cognitive tasks under single- and dual-task conditions, designed to challenge their focus of attention with acoustic and visual stimuli and specific executive functions. Furthermore, exercises for strength, balance and flexibility as well as endurance performance associated with walking are integrated.

To ensure a controllable structure, training sessions are divided in five parts: 1. 5–10 min mobilisation and warm-up (e.g., range of motion exercises for the wrists, hip, shoulders, knees, and ankles). 2. 10 min coordination, balance, and cognitive exercises (e.g., standing balance, bodyweight shifting, motivational cognitive-motor games with group interaction including balls and scarfs). 3. 20 min aerobic walking exercises (e.g., under different single and dual-task conditions). 4. 10 min strength exercises (e.g., chair rises, upper body and trunk exercises with additional materials and weights, functional lower-limb exercises). 5. 5–10 min calm down (e.g., stretching and relaxing exercises).

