#### Sample size estimate / power calculations

The required sample size was calculated with G*Power (Version 3.1.9.2, Heinrich Heine University of Duesseldorf) [62]. The sample size calculation was approximated with a 2 × 3-factorial analysis of variance (ANOVA) for repeated measures (within-between interaction, small effect size, power of .80 [1-β], 2-sided α-error (95% CI), 2 groups, 3 measurements) based on the primary outcome Short Physical Performance Battery (SPPB). The small effect size used for the calculation of required sample size is based on literature reviews and assumptions of clinically relevant changes for residents in nursing homes with probable cognitive impairment [63]. One hundred eight individuals per region are required in order to detect a clinically meaningful change of ≥1.0 point with a SD of 0.99 points. To account for potential dropouts before study completion, we will inflate the sample size by 30% (20% losses during follow-up; 10% mortality), resulting in a total sample size of 1120 individuals (140 per centre with 70 participants allocated to each group).

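### The allocation rule names sex, age and MoCA but no level at which the lot is drawn, so it does not secure the stated 70:70 per centre and leaves the split within each nursing home to chance

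*Protocol article*

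**What the plan says.** All references are to the protocol article.

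- **Assignment of interventions.** Individuals are randomised; the aim is to "divide the participants into either an intervention group or a waiting time control group". The allocation is "executed by lot by the director of the study who will receive the pseudonymized codes of the participants and their baseline characteristics". The factors are listed: "Stratification will be based on comparable sex, age, and cognitive performance", with cognition measured by the MoCA. Neither home nor centre is on the list.
- **Trial design.** The stratified randomisation follows the baseline assessment.
- **Sample size estimate / power calculations.** The inflated target is stated as "resulting in a total sample size of 1120 individuals (140 per centre with 70 participants allocated to each group".
- **Recruitment of nursing homes.** There are 48 homes, six per site, chosen to differ in number of places, staffing, district and socio-economic status, "in order to analyze the applicability of the program under a wide range of conditions".
- **Intervention.** Training is delivered in groups, "with group sizes ranging from four to 15 participants".
- **Physical functioning (primary outcomes).** Gait is measured "using of one of the mentioned gait analysis systems". Five systems are listed, none is tied to a site, and a validation study is announced.
- **Statistical analysis.** Between-group differences are adjusted for baseline value, age, sex and education. Home and centre are not among the covariates.

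**The concern.** The article gives a positive list of stratification factors, and that list does not by itself produce the per-centre split on which the sample size section relies. The two sections agree only if the lot is run separately in each centre, and the allocation section does not say so.

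Home is a second gap, which neither reading closes. Homes are selected to be unlike one another, and training takes place in small groups. Staffing, case mix and the usual physiotherapy that the protocol permits can plausibly differ between homes. If the numbers per arm drift within homes, some between-home variation enters the treatment contrast as noise, and the stated covariates do not take it out. Individual homes may also end with an arm that does not fit one training group.

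**Working it through.** **Inputs.** 108 required per region and 30% inflation (sample size section); 8 centres and 48 homes, six per site (recruitment section); groups of 4 to 15 (intervention section); strata of sex, age and MoCA (allocation section).

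**The plan's own figure.** 108 × 1.3 = 140.4, taken as 140 per centre; 140 × 8 = 1120; 140 / 2 = 70 per arm per centre. The stated total and split reproduce.

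**Average home.** 140 / 6 = 23.3 residents, or 70 / 6 = 11.7 per arm.

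**Split per centre.** If n residents belong to a pool of M that is divided exactly in half, the number allocated to intervention is hypergeometric, with variance n × ½ × ½ × (M − n)/(M − 1).

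- *Lot pooled over all centres* (M = 1120, n = 140): SD = √(35 × 980/1119) = 5.5; 95% range 59 to 81; exactly 70:70 has probability 7%. A simulation that applies eight equally likely sex/age/MoCA strata (4000 runs) also gives 7%, so the named strata do nothing for centre balance.
- *Lot run separately in each centre* with the same strata: simulated SD about 0.9, so 70:70 is essentially met.

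**Split per home.** The same formula with n = 23 or 24:

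| Lot drawn | SD, 23 residents | SD, 24 residents | P(intervention arm > 15), 23 / 24 residents |
|---|---|---|---|
| per centre (M = 140) | √(5.75 × 117/139) = 2.20 | √(6 × 116/139) = 2.24 | 3.3% / 5.8% |
| pooled (M = 1120) | √(5.75 × 1097/1119) = 2.37 | √(6 × 1096/1119) = 2.42 | 4.5% / 7.4% |

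The probability of fewer than 4 is below 0.1% throughout, so at this home size only the upper limit matters. In the simulation (48 homes of 23 or 24), 4.2% of homes (per centre) to 5.4% (pooled) have an intervention arm outside 4 to 15. That is 0.042 × 48 = 2.0 to 0.054 × 48 = 2.6 homes. At least one home is affected in 89% to 96% of simulated trials.

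**Sensitivity to home size.** The article gives no enrolment per home. With 12 residents, P(< 4) is 6 to 7%; with 20, P(> 15) is 0.3 to 0.6%; with 28, P(> 15) is 26 to 28%.

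**Loss of precision.** If home is fitted as a fixed effect, a home with k of n on intervention contributes information proportional to k(n − k)/n. Its expected shortfall against an even split is 4 × Var(k)/n². For n = 23 this is 4 × 2.20²/529 = 3.7% (per centre) to 4 × 2.37²/529 = 4.2% (pooled).

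**After the change.** With 1:1 drawn within each home, a home of 24 gives 12 and a home of 23 gives 11 or 12. A centre of two homes of 24 and four of 23 then has 24 + 44 = 68 to 24 + 48 = 72 on intervention. No home of this size falls outside 4 to 15.

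**The case against.** The best defence is that silence is not exclusion. A journal article may leave the mechanics of the draw to the full protocol, and the per-centre figure reads naturally as 1:1 allocation run in each centre. That much stands: the article does not prove that centre is ignored, and the centre point is one of reconciling two sections. It does not dispose of the point, because the article gives an affirmative list of factors that omits both levels, and nothing in it covers home.

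A reader might infer that arm is confounded with home or with gait device. The documents do not support that. Individuals are randomised, both arms are expected in every home, and any imbalance is chance. No gait system is tied to a home or site, so the device argument applies only if each keeps one system. Even then, a centre split 81:59 carries only (81 − 59)/560 = 3.9% of its device offset into the arm difference. Baseline adjustment removes an additive offset if a participant's device does not change, and the validation study addresses comparability.

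The group-size argument is also limited. The article does not say that each home runs one group, and it plans a seated programme for residents who cannot walk, so a large arm could be split. Counting the waiting-list arm as well would bring the simulated figure to about 4 to 5 homes, but that arm trains only after the 16-week comparison and after some attrition.

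Finally, blocking by home makes fine balance on sex, age and MoCA harder. That is a real cost.

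**Conclusion.** The point holds as a design choice that can be improved cheaply and as two sections to be reconciled; it is not a threat to validity. The allocation rule as written does not secure 70:70 per centre: the 95% range is about 59 to 81 if the lot is pooled, and the split is essentially met if it is run per centre. On either reading the split within homes is left to chance, with SD about 2.2 to 2.4 around an expected 11 to 12. The consequences are modest: roughly 4% of precision if home is modelled, and 4 to 5% of homes with an intervention arm outside a single group of 4 to 15.

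These figures assume equal home sizes of 23 or 24, one training group per home, and eight equally likely strata unrelated to home. Unequal home sizes, which the selection of homes makes likely, would change the group-size figure considerably in either direction. The precision figure assumes home as a fixed effect.

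**What to change.** In Assignment of interventions, state that once a home's baseline assessments are complete, the 1:1 allocation is drawn separately within that home, with home as the block. Sex, age and MoCA are then balanced within the home by coarse categories or by minimisation. This brings the section into line with the per-centre figure in the sample size section, to within about 2 per centre. It would also balance the gait system if each home keeps one. In Statistical analysis, add home or centre to the mixed model so that the analysis matches the allocation.

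**Cost.** The total stays at 1120, and the step already follows baseline assessment, so no extra staff or data are needed. Balance on the three named factors becomes coarser: two levels of each make eight cells, and 23.3 / 8 leaves about 3 residents per cell if home is fully crossed with them. Minimisation would replace simple drawing of lots. The group-size range is still not guaranteed at the extremes: an even split of 6 residents gives 3 per arm, and of 32 gives 16.
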